## Abstract

**Background:**

Parental supervised brushing (PSB) when initiated in infancy can lead to long-term protective home-based oral health habits thereby reducing the risk of dental caries. However, PSB is a complex behaviour with many barriers reported by parents hindering its effective implementation. Within the UK, oral health advice is delivered universally to parents by health visitors and their wider teams when children are aged between 9 and 12 months. Nevertheless, there is no standardised intervention or training upon which health visitors can base this advice, and they often lack the specialised knowledge needed to help parents overcome barriers to performing PSB and limiting sugary foods and drinks.

Working with health visitors and parents of children aged 9–24 months, we have co-designed oral health training and resources (Health Visitors delivering Advice in Britain on Infant Toothbrushing (HABIT) intervention) to be used by health visitors and their wider teams when providing parents of children aged 9–12 months with oral health advice.

The aim of the study is to explore the acceptability of the HABIT intervention to parents and health visitors, to examine the mechanism of action and develop suitable objective measures of PSB.

**Methods/design:**

Six health visitors working in a deprived city in the UK will be provided with training on how to use the HABIT intervention. Health visitors will then each deliver the intervention to five parents of children aged 9–12 months. The research team will collect measures of PSB and dietary behaviours before and at 2 weeks and 3 months after the HABIT intervention. Acceptability of the HABIT intervention to health visitors will be explored through semi-structured diaries completed after each visit and a focus group discussion after delivery to all parents. Acceptability of the HABIT intervention and mechanism of action will be explored briefly during each home visit with parents and in greater details in 20–25 qualitative interviews after the completion of data collection. The utility of three objective measures of PSB will be compared with each other and with parental-self reports.

**Discussion:**

This study will provide essential information to inform the design of a definitive cluster randomised controlled trial.

**Trial registration:**

There is no database for early phase studies such as ours.

## Background

Dental caries (tooth decay) is the most prevalent preventable childhood disease and a major public health priority [1, 2]. In England, 12% of 3-year-olds and 25% of 5-year-olds are affected by caries, with figures rising to 17 and 37% for children living in deprived parts of Yorkshire [3].

Caries has a significant effect on a child, their wider family and society. In the short term, a child whose teeth are affected by caries is likely to experience pain and discomfort [4], as well as dietary changes [5, 6], and in the long term, caries may have a negative impact on speech development [7], overall health [8], quality of life [9, 10], self-esteem and social confidence [9, 11]. It also has a wider societal impact on school readiness, attendance and educational outcome [12, 13]. The cost of managing dental caries in children is substantial and accounts for a significant proportion of the £3.4 billion annual spend on NHS dentistry [14]. Caries is the most common reason for young children (over 30,000 children) to be admitted to hospital for dental care under general anaesthetic with this alone costing the NHS approximately £36 million a year [15].

Since 2012, local authorities have had a statutory requirement to commission community-based oral health promotion programmes as well as the Health Child programme. Caries prevalence in 5-year-olds is included as a key priority in the Public Health Outcomes Framework [1]. Recent NICE [16] and Public Health England [15] guidance to local authorities has recommended early-life interventions to prevent caries. One of the opportunities through which parents may engage with oral health advice is via health visitors [17, 18]. In England, health visitors and their wider teams carry out universal home visits to families when children are aged 9–12 months. Many topics are discussed at this visit including nutrition and obesity prevention, child development (including speech, language and communication), safety and oral health [19]. In some localities, these visits include the provision of a tube of fluoride toothpaste and a toothbrush. While public health guidance [14, 19] advocates the benefits of improving home-based oral health behaviours at these visits, they also identify the limited evidence of the effectiveness of these oral health conversations. Furthermore, while data from the UK is scarce, studies conducted in the US suggest that often health visitors themselves lack knowledge about oral health and diet, and skills in how to support parents to adopt protective home-based oral health behaviours for their child [20]. Limited and often absent provision of resources and training prevents health visitors from effectively communicating oral health messages [20]. Therefore, it is not surprising that health visitors often lack confidence, which prevents them from engaging more actively in oral health promotion, fulfilling their professional role [17] and shaping the foundation for children’s good oral health.

A key home-based protective oral health behaviour is toothbrushing. National guidance, for children aged 0–3 years old, recommends twice daily parental supervised brushing (PSB) with a smear of fluoride toothpaste (at least 1000 ppm) initiated from the eruption of the first tooth (around 6 months old) [21]. We will use the term parental supervised brushing (PSB) to summarise this collection of behaviours. PSB is a highly effective evidence-based approach and, where adopted, dramatically reduces early childhood caries by approximately 30% with these benefits maintained into adulthood [22–24]. Toothbrushing practices are predominantly clustered within family-based traditions with additional wider cultural influences [25]. Establishing this routine behaviour is best inculcated in infancy by the parents [25]; it is a life skill which if initiated in infancy and becomes habitual is a strong predictor for future oral health [23]. However, the adoption of PSB frequently fails [24] as it is a complex dyadic behaviour with many barriers to adoption [26, 27]. Previous interventions to encourage PSB have been simplistic and failed to recognise the complexity of this behaviour [27]. A lack of PSB is one of the reasons why caries prevalence in children and children remains unacceptably high [24].

A key focus of the Health Visitors delivering Advice in Britain on Infant Toothbrushing (HABIT) interventions is improving PSB in infancy. Advice around limiting sugary foods and drinks is also included. The HABIT intervention is underpinned by a logic model [28]. This describes what barriers to PSB need to be addressed and how this will lead to changes in motivation to undertake PSB and then an increase in PSB being undertaken. This increase in PSB leads to a reduction in early childhood caries. Whilst there are robust measures of dental caries, these require long-term follow-up (a minimum of 3 years) and are consequently more expensive [29–31]. While short-term parental-self reports of PSB exist, these are at high risk of social desirability bias. The size of this bias and the lack of objective proxy measures that robustly characterise PSB behaviour is a key evidence gap that will be addressed in this study.

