### Aims of study

This study, through working with health visitors and parents of children aged 9–12 months, aims (i) to explore the acceptability of the HABIT intervention to health visitors and parents of children, (ii) to examine the mechanism of action of the HABIT intervention on PSB adoption and maintenance and (iii) to develop a suitable objective measure(s) of PSB adoption.

Using a mixed-methods approach, it will specifically:Explore how the HABIT oral health intervention works in practice and how it influences behaviour changeIdentify intervention mechanisms that are most likely to lead to the adoption of PSB within the daily routineEstablish the acceptability of the HABIT oral health intervention to parents and health visitorsDevelop and correlate different objective measures of toothbrushing with parental self-reports of PSB

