#### Data collection

Data will be collected about the following variables: sociodemographic characteristics, effectiveness of current toothbrushing, duration and parent/child interaction during toothbrushing, toothbrushing activity, self-reported toothbrushing and dietary behaviours, acceptability of the HABIT intervention and qualitative enquiry to explore mechanism of action.

Data collection with parents will consist of at least three rounds:First round—*Baseline data collection*. In the home setting, baseline PSB data will be collected before the universal home visit provided by the HABIT-trained health visitor. A researcher will ask validated questions of parents about their PSB habits, e.g. self-reported PSB [24] including questions about brushing frequency, use of fluoride toothpaste, parental involvement, and age of initiation. Three different proxy objective measures of PSB will be collected:Effectiveness of current toothbrushing—children pre-brushing plaque levels on the buccal surface of each erupted primary tooth will be quantified using an established index [38];Duration and parent/child (dyad) interaction during toothbrushing—the researcher will film the dyad toothbrushing and this will be subsequently evaluated by the HABIT research team using an established PSB index [39];Toothbrushing activity—parents will be provided with a regular children toothbrush in conjunction with a Magic Timer app for their phone/tablet which monitors frequency and duration of children brushing. Magic Timer app is freely available on the Internet for members of the public. For parents who do not have or are unable to use devices providing access to the app, a hard copy of the Magic Timer diary with aspects of the Magic Timer app will be provided.

For measuring plaque level, a food colouring agent will be used and then wiped away. In cases where children are allergic to a food colouring agent or parents refuse these to be used, pre-brushing plaque levels will not be measured. The activity will be carried out either at the parent’s home setting or a health care setting where they normally see a health visitor. The baseline data collection will approximately take 30–45 min.

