
#### Data analysis

This study will produce three objective measures (a-c) which aim to quantify the underlying latent concept of PSB. These will be combined with a ‘measurement model’ (see Fig. 1) as it is referred within the structural equation modelling literature. It is anticipated that as the quality of PSB increases, the three objective measures will increase. The latent variable PSB will capture those components which co-vary. That is, PSB will quantify the covariance of the objective measures.

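### The Background says the study will address the size of the self-report bias, but correlation, the only stated link to self-report, cannot measure it

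*Protocol article*

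**What the plan says.** The Background sets up the problem: "While short-term parental-self reports of PSB exist, these are at high risk of social desirability bias". The next sentence begins "The size of this bias and the lack of objective proxy measures that robustly characterise PSB behaviour is a key evidence gap" and ends by saying that the study will address this gap.

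The abstract states: "The utility of three objective measures of PSB will be compared with each other and with parental-self reports". Under Aims of study, the fourth specific objective is to develop and "correlate different objective measures of toothbrushing with parental self-reports of PSB". The Discussion repeats the intention in similar terms.

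The parent Data collection section describes the self-report questions as "including questions about brushing frequency, use of fluoride toothpaste, parental involvement, and age of initiation". It lists three objective measures: (a) plaque level, (b) a filmed brushing session scored on an index, and (c) brushing activity from the "Magic Timer app for their phone/tablet which monitors frequency and duration of children brushing". Families who cannot use the app receive a paper diary instead. Self-report and all three objective measures are collected again at 2 weeks and 3 months.

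The parent Data analysis section builds a measurement model from measures a to c ("The latent variable PSB will capture those components which co-vary"), then a growth model on that latent variable over 0, 2 and 12 weeks. The standardised loadings are used to rank the three measures. Self-report is not mentioned in that section.

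**The concern.** The size of a bias is a difference in level: how many more brushings per day parents report than take place. None of the stated analyses yields a difference in level between self-report and an objective measure. The models contain no self-report variable, and correlation measures only how far two quantities rise and fall together.

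Two things are at stake. The study could finish without an answer to a question that its Background says it will address. A good correlation could also be read as support for self-report as an outcome in the later trial, even if the reported level were well above the true one.

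**Working it through.** The article gives no figure for the bias or its precision, so there is none to reproduce. The check has three steps.

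**1. Tracing self-report through the article.**

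| Place | Role of self-report |
|---|---|
| Background | Size of its bias is part of the gap to be addressed |
| Abstract, Discussion | To be set against the objective measures; no quantity defined |
| Aims of study | To be correlated with the objective measures |
| Data collection (parents) | Collected at baseline, 2 weeks and 3 months |
| Data analysis (parents) | Not mentioned; the models use measures a to c |

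Correlation is therefore the only stated method connecting the two.

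**2. What correlation can show.** Let X be the objective value, Y the self-report and b a constant over-report. Adding b changes neither the covariance nor the standard deviations, so corr(X, Y + b) = corr(X, Y). The mean difference, in contrast, rises by exactly b. In one simulated sample of 30 pairs (arbitrary units):

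| Constant over-report b | Correlation | Mean difference |
|---|---|---|
| 0 | 0.602 | 0.0 |
| 2 | 0.602 | 2.0 |
| 4 | 0.602 | 4.0 |
| 8 | 0.602 | 8.0 |

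The association itself would also be imprecise. With n = 30 and an observed r of 0.5, the Fisher interval is tanh(atanh(0.5) ± 1.96/√27) = tanh(0.549 ± 0.377), or 0.17 to 0.73.

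**3. What a paired difference could show.** Brushing frequency is the one quantity that the article describes as both self-reported and recorded objectively on the same scale. The 95% half-width for a mean paired difference is t(0.975, n − 1) × SD/√n. The article gives no SD of differences, so 0.6 and 1.0 brushings per day are assumptions that show a range. The number of app users is also unknown; 30 is the maximum (6 health visitors × 5 parents).

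| App users | Half-width in SD | If SD = 0.6 | If SD = 1.0 |
|---|---|---|---|
| 30 | 2.045/√30 = 0.37 | 0.22 | 0.37 |
| 25 | 2.064/√25 = 0.41 | 0.25 | 0.41 |
| 20 | 2.093/√20 = 0.47 | 0.28 | 0.47 |

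These figures treat parents as independent. Clustering within the six health visitors could widen them.

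**The case against.** The strongest reply has four parts.

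- **The comparison is planned.** A reader might infer that the objective measures are never compared with self-report, or that the fourth objective ends without an estimate. The article does not support that. The objective names correlation, and a correlation coefficient is an estimate of association. This part of the reply stands.
- **The article is condensed.** It describes the less usual models and could leave a simple correlation to a fuller plan. Nothing in the Data analysis section says that self-report is excluded from all analysis. This also stands, so the silence of that section is not the defect. The defect is that the one method named cannot yield the quantity the Background refers to.
- **The bias size appears in one Background sentence and not among the formal aims.** This is true and limits the weight of the point. The sentence still says that the study will address the gap, and withdrawing it is one acceptable remedy.
- **The app log is not a reference standard.** A reader might conclude that, with 30 families, the bias itself can be estimated to within 0.22 brushings per day. That is not supported. The figure needs all 30 parents to use the app and an assumed SD of 0.6. Self-report minus app log also mixes over-reporting with sessions that were not logged, and nothing described in the article separates the two. In addition, the app is handed out at the baseline visit, so no app record that matches the baseline self-report is described. All of this stands and shapes the remedy.

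Plaque and the film index share no unit with self-reported frequency. For those two measures correlation is a reasonable choice, and the criticism applies only to its use as a route to the size of the bias.

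**Conclusion.** The point holds in a limited form. The Background commits the study to addressing the size of the self-report bias, and the only stated link between self-report and the objective measures, correlation, is blind to a constant over-report. The latent-variable models do not fill the gap because they use measures a to c only. As written, the article leads to an estimate of association and none of bias.

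The data allow a partial repair: a discrepancy in brushings per day among app users. Its precision depends on how many parents use the app, on the assumed SD of differences and on the absence of clustering. Even if precisely estimated, the discrepancy would lean towards overstating the bias because of missed logging.

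**What to change.** Add a short paragraph to the analysis plan:

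1. At 2 weeks and 3 months, among parents using the app, report the mean paired difference (self-reported minus app-logged brushings per day) with a 95% confidence interval and limits of agreement. State the logging window. Include baseline only if a logging window is defined for it.
2. Leave out families using the paper diary, because it is completed by the parent and is not an objective record. Report how many families this removes.
3. Call the result the discrepancy between self-report and app log, an upper-leaning indication of over-reporting because missed logging inflates it.
4. Keep correlation for plaque and the film index, and describe it as association.

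If this analysis is not wanted, withdraw the Background statement on the size of the bias.

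The cost is one paragraph. The article already provides for both quantities to be collected at the two follow-up rounds, so no new instrument or visit is needed.

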### HABIT resources for an oral health intervention

Our multi-disciplinary research team together with health visiting teams and parents of children aged 9–24 months have collaborated to co-design training and materials to support oral health discussions between parents and health visitors with the aim of maximising the uptake of appropriate home-based oral health behaviours, including PSB adoption. We have called the intervention HABIT and it has been developed using the following methodology. Using professional contacts, we have collected examples of materials that have been already developed for health visitors to support their oral health conversations across England.^1^ We have then discussed these materials with parents and health visitors in a series of focus groups and interviews to identify which are most likely to lead parents to adopt appropriate oral health behaviours. These conversations have informed the development of the HABIT intervention in conjunction with our extensive research [26, 28, 32] which has followed the complex intervention development framework laid out by the MRC [33]. The intervention consists of two packages: (A) training for health visitors to deliver the HABIT intervention and (B) HABIT resources for parents.

The training for health visitors covers areas such as general oral health messages and knowledge related to toothbrushing and diet, as well as an introduction to additionally available oral health resources. We intend to use already available resources which comply with national guidance [21] such as SOAP videos (http://www.soap.media/our-courses/letstalkaboutteeth/) and the NHS e-learning package http://www.e-lfh.org.uk/programmes/healthy-school-child/. The 1-day training will also include training around how to effectively use HABIT resources to enable behaviour change conversations with parents.

The HABIT resources for parents aims to support them to adopt and maintain good oral health practices for their children and to tackle barriers that prevent them from achieving this goal. The provided resources will focus on aspects such as ‘Why is oral health important?’, ‘How to adopt protective home-based oral health behaviours?’ and ‘When to start these oral-health behaviours?’ The HABIT intervention will include short video vignettes, provision of a toothbrush and toothpaste and simple advice sheets on issues such as oral health knowledge and skills, managing children’s behaviour and the wider social environment as well as, knowledge about diet. The video vignettes include a mixture of parent stories and professional advice.

### Aims of study

This study, through working with health visitors and parents of children aged 9–12 months, aims (i) to explore the acceptability of the HABIT intervention to health visitors and parents of children, (ii) to examine the mechanism of action of the HABIT intervention on PSB adoption and maintenance and (iii) to develop a suitable objective measure(s) of PSB adoption.

Using a mixed-methods approach, it will specifically:Explore how the HABIT oral health intervention works in practice and how it influences behaviour changeIdentify intervention mechanisms that are most likely to lead to the adoption of PSB within the daily routineEstablish the acceptability of the HABIT oral health intervention to parents and health visitorsDevelop and correlate different objective measures of toothbrushing with parental self-reports of PSB

## Methods/design

This mixed-methods study will involve two participant groups: (A) health visitors (*n* = 6) and (B) parents of children aged 9–12 months (*n* = 30) to allow the objectives to be achieved and to capture the perspectives of all relevant stakeholders. For each participant group the design, procedure and approach to data collection and analysis will be described.

### Acceptability of the HABIT resources for health visitors

#### Design of the study

This part of the study will test the acceptability of the HABIT resources for health visitors undertaking a universal home visit to families of children aged 9–12 months. Firstly, recruited health visitors will be trained to deliver the HABIT intervention. This training will include an update on oral health to ensure all health visitors provide uniform evidence-based advice [21], training on how to use the HABIT resources and discussions on how to engage with parents in a behaviour change conversation. After receiving the training, each of the health visitors will undertake an oral-health conversation using the HABIT resources to five parents of children aged 9–12 months during the universal home visit. After each home visit, the health visitors will complete a semi-structured diary where they will reflect on parents’ child toothbrushing habits and their reaction and response to the HABIT resources as well as their own experience when using these resources.

Once all six health visitors have delivered the intervention, they will participate in a focus group. A topic guide will be used as the framework for the discussion and will shed light on the received training and experience of using the HABIT intervention for parents, its strengths and weaknesses as well as whether it fits everyday professional practice. Focus group discussion will provide deeper and broader insight into why certain opinions, positions and perspectives are held [34] and the issues that may prevent or facilitate implementation of the intervention [35]. The topic guide has been developed based on Ayala et al.’s [35] definition of acceptability and Gray-Burrows et al.’s [28] model for intervention mapping to develop a home-based PBS intervention for young children. The two frameworks will enable the exploration of the acceptability of the HABIT intervention as well as key barriers and facilitators (e.g. knowledge, skills, confidence and attitudes), which may influence health visitors’ experience and intentions to use the resources. The focus group will be digitally recorded and professionally transcribed after the event. The recording will be deleted after accuracy of the transcription and recording is checked. All identifying information will be removed from the transcripts to ensure anonymity.

